#### Questionnaires summary

There are 12 questionnaires/surveys: PSQI, IPAQ-SF, EQ-5D-3L, IWQOL-Lite, WEMWBS, PHQ9, GAD7, PoF, CoEQ, COM-B healthy eating and PA questionnaire, Intake24 and EPIC-Norfolk FFQ. Time points for completion are detailed in table 4 and in online supplemental material 5.

**Table 4 T4:** Time points of questionnaires in the UPDATE trial

Visit	No of questionnaires	Time to complete
Screening	Intake 24 only	12 min
RCT: First baseline visit Behavioural intervention: 6 months follow-up (visits 2 and 9)	All 12 questionnaires	90 min
RCT: Week 4 Week 8 Second baseline visit (visits 3, 4, 5, 6 and 7)	11 questionnaires (all except the COM-B healthy eating and PA questionnaire)	60 min

COM-B, Capability, Opportunity, Motivation-Behaviour; PA, physical activity; RCT, randomised controlled trial; UPDATE, Investigating the effects of Ultra-Processed versus minimally processed Diets following UK dietAry guidance on healTh outcomEs.

#### Feasibility/acceptability and process evaluation of the behavioural intervention

Feasibility/acceptability and process evaluation will be described in full in the subsequent paper focused on the behavioural intervention. However, the main feasibility/acceptability outcome will be the percentage of intervention calls successfully delivered, as well as retention to the study. For quality control intervention calls will be recorded and coded against a checklist to ensure that target BCTs are being delivered as planned. Acceptability of the intervention content and process will be gathered in qualitative interviews. Changes in other outcomes pre and post the behavioural intervention will be explored as secondary.

#### Qualitative interviews

In the first behavioural intervention call, before being told that the intervention(s) focus on processing, participants will be asked to describe their experiences of each of the trial diets 1A/2B (positives and negatives, how they felt physically/mentally, barriers they faced to adherence) then probed on which diet they thought was UPF versus MPF and why. In addition, at the end of the behavioural intervention, participants will be invited to take part in a one-to-one semistructured telephone interview about their experiences of the trial overall, motivations for participation, barriers to reducing UPF and increasing MPF, and experience of the behavioural intervention specifically (whether they found materials and process acceptable/useful).

### Data methods: monitoring

#### Data monitoring

Data generated from this trial will be handled (including collection, storage, processing and disclosure) in accordance with all applicable legal and regulatory requirements, including the UK Data Protection Act (DPA) 2018 and European Union General Data Protection Regulation (EU GDPR 2016/679). All members of the research team are trained in information governance and research integrity.

All data storage mediums will comply with the NHS Information Governance Toolkit. All physical data will be stored in a secure room, with limited access only to members of the research team. All computers storing electronic data will be encrypted and password protected. Data will be first stored on paper case report forms (CRF), securely kept in a locked cabinet in a locked office and then recorded electronically on a purpose-built trial database (eCRF) using the REDCap system (https://www.project-redcap.org). REDCap is hosted within the UCL Data Safe Haven, a ISO27001 certified secure environment protected by dedicated firewalls, accessed by role-based user accounts with multifactor authentication. Each participant has their own eCRF, listed under their participant identification number (PIN). Questionnaires will be provided electronically and stored directly in REDCap. The REDCap database contains range validity checks with warnings for erroneous or missing values, and initial data entry from the paper CRF will be verified by a second team member for quality assurance. The REDCap application also provides a comprehensive audit trail showing all changes to the data.

Data confidentiality is outlined in the PIS (online supplemental material 1). Participant initials and their PIN will be used on records. The CRF will not bear the participant’s name or other personal identifiable data. Identifiable information will be stored in a separate electronic database to the database containing trial data. Participants’ personal identity and data collected in the study cannot be connected by anyone outside the study team. The data generated from this trial will not be transferred to any party not identified in the protocol and will not be processed and/or transferred other than in accordance with the participants’ consent. Confidentiality will be maintained by user agreements prior to access, ensuring all researchers uphold the principles of Good Clinical Practice (GCP), EU GDPR 679/2016 and DPA 2018.

### Retention

Loss to follow-up will be minimised through weekly telephone calls during the RCT and monthly calls during the 6-month behavioural intervention to discuss any issues and adherence, encouraging participants to discuss any difficulties with researchers. Other procedures will be adopted for maintaining participation in the study (eg, reminders before scheduled trial visits, sending greetings messages, personalising letters and keeping measures short in terms of completion time). No data will be collected after withdrawal.

### Sample size

The sample size of 55 is based on^21^ showing 0.9 kg weight loss following a 2-week MPF diet, with an SD of the mean difference in weight change of 1.98 kg between MPF and UPF diets (mean: 1.85 kg), the predicted weight loss if the MPF diet were continued for 8 weeks (using the NIH bodyweight planner (https://www.niddk.nih.gov/bwp)).

No interventional studies to date have compared diets differing in the nature, extent and purpose of food processing over this duration. To best estimate the expected difference in %WC over this time frame, the results from the only controlled feeding trial comparing UPF and MPF diets matched for diet quality on weight change were used,^21^ which lasted for 2 weeks. Inclusion criteria for UPDATE require participants to have a habitual diet high in UPF, thus the UPF diet is hypothesised at best to lead to no change in weight. Whereas, the MPF diet will result in weight loss, with a similar initial trajectory to that in Hall *et al*.^21^ The NIH bodyweight planner takes into account that weight change is not linear based on the initial calorie deficit and tends to plateau and considers key factors that influence metabolic rate. The mean age, height, weight and PA levels of the male and female participants from Hall *et al* were entered into the bodyweight planner to produce a quantitative estimate of weight change on the MPF diet over 8 weeks, which was converted percentage weight change. Male participants in Hall *et al*
21 would achieve 2.8% (2.2 kg) weight loss after 8 weeks on the MPF diet, and female participants would achieve 2.7% (2.1 kg) weight loss. There is no clear value from the literature as to what the SD should be for the mean difference in weight change between 8 week MPF and UPF diets. The expected SD must, therefore, be estimated. The 1.98 kg value for the SD of the mean difference in weight change from Hall *et al* was used as the starting point for the expected SD after 8 weeks. This was around 1.1× the mean difference in weight change between MPF and UPF diet interventions. By assuming that the SD would increase over 8 weeks compared with 2 weeks, the SD was assumed to increase to 2× the mean difference in weight change between MPF and UPF diets. Other trials longer in duration than Hall *et al* were considered, but other trials have a number of fundamental differences to the planned trial, which limits the ability to extrapolate their findings (eg, not necessarily ad libitum or cross-over trials, testing diets that are unrelated to the concepts of MPF or UPF, or comparing an intervention to a control diet, (whereas UPDATE involves two interventions)). These generally reported SDs for the mean weight change of each group, rather than of the mean difference between groups. For each group over several weeks (eg, 12 weeks), the SDs tended to be around 0.1–0.9× the mean weight change. Therefore, the Hall *et al*’s estimate was considered most applicable, relevant and conservative.

Assuming weight loss on the MPF diet and no weight change on the UPF diet, 44 participants are required to detect a mean difference of 2.7% weight change between diets (SD of 5.4% (2× the mean difference), power=0.9, alpha=0.05, with a two-sided paired t-test, using SPSS V.27.0). With a 20% drop-out rate based on previous controlled feeding trials,^81 82^ 55 participants will be recruited. This is comparable to attrition rates in previous multiarm, community-based cross-over trials lasting several months, where participants are provided with all meals.^83–86^

The target sample size for the qualitative interviews is 20–30. Data saturation is controversial, but researchers will aim for meaningful saturation, whereby further interviews produce minimal, or no changes to the coding framework and allow complete understanding of thematic codes.^87^ Where possible, participants will be selected to ensure representation from across ethnicities, night shift patterns, genders, treatment allocation arms. All participants will be offered the behavioural intervention calls, so will be asked about experiences of the provided trial diets.

### Statistical methods

A Consolidated Standards of Reporting Trials (CONSORT) diagram and descriptive statistics will be used to outline the trial sample.^88^ The primary outcome will be analysed using mixed-effects models, with a random effect for participants, adjusting for stratification variables and any baseline variables not balanced between arms. Age will also be included as an adjustment covariate. An intention-to-treat analysis will be conducted,^89^ with values presented by randomisation group and all available data analysed as randomised. Additional models will include a per-protocol analysis, and repeated-measures analysis additionally using data from 4 week follow-ups. Bias from missing data will be dealt with using multiple imputation.^90^ The 4-week washout period between diets will minimise any carryover effects,^88^ with any residual effect assessed between arms. To account for non-adherence (consuming more than one meal per week off the intervention diet), inverse probability weighting will be used to reweight the remaining sample.^91^ There is no planned interim analysis.

Secondary outcome variables for the RCT and behavioural intervention will be analysed using mixed-effects or linear, binary or ordinal regression models, where appropriate.

Qualitative interviews will be analysed using framework analysis, following the stages outlined by Gale *et al*.^92^ Transcripts will be deductively coded, broadly mapping barriers and facilitators to the COM-B model^36 37^ and TDF^38^—an approach previously used to understand the experience of novel diets,^93^ as well as inductively coding aspects that may not naturally fit into these groupings. Recordings will be converted into text using transcription software. Two researchers will initially independently analyse three interviews, before meeting to discuss and develop an initial framework. Additional transcripts will then be coded based on this framework, with additional factors added as they arise. Two researchers will interpret data and write the report in accordance with the consolidated criteria for reporting qualitative research checklist (www.equator-network.org/reporting-guidelines/coreq).

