### Objectives and hypotheses

To date, no studies have assessed whether the health impact of following dietary guidelines is dependent on food processing, nor whether providing behavioural support to UK adults living with overweight/obesity can help to reduce their UPF intake.

Therefore, this study aims to compare the health effects between MPF and UPF diets that follow the EWG recommendations, and the feasibility and acceptability of a behavioural support programme to reduce UPF intake and be more physically active.

The primary objective is to compare weight change between MPF and UPF diets following EWG recommendations (table 1). Secondary objectives are to compare changes in cardiometabolic, behavioural, mental and hormonal outcomes between MPF and UPF diets following EWG recommendations and explore the feasibility and acceptability of the behavioural support intervention.

**Table 1 T1:** UPDATE trial design based on PICOT

Population	Adults (UCLH staff) living with overweight or obesity, and with ≥50% of habitual energy intake from UPFs
Intervention	A minimally processed diet complying with UK EWG guidance
Comparator	An ultra-processed diet complying with UK EWG guidance
Outcome (primary)	Mean difference in percent weight change between intervention and comparator at 8 weeks
Timepoints	Primary outcome assessed from baseline to 8 weeks follow-up on each diet

EWG, Eatwell Guide; UCLH, University College London Hospitals; UPDATE, Investigating the effects of Ultra-Processed versus minimally processed Diets following UK dietAry guidance on healTh outcomEs; UPF, ultra-processed food.

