### Outcomes

Outcome measures will be collected at seven in-person visits. See figure 1 and online supplemental material 5 for the schedule of assessments.

10.1136/bmjopen-2023-079027.supp5Supplementary data

The primary outcome is the mean difference in percent weight change (%WC) at 8 weeks from baseline between MPF and UPF diets. This outcome is currently being used clinically in weight management clinics and used for all NHS weight management programmes. Clinically significant weight change can occur from short-term dietary interventions and directly relates to improvements in cardiometabolic risk factors (eg, blood pressure, blood glucose, glycated haemoglobin (HbA1c), lipids),^42^ physical function and quality of life.^43^ Weight is an efficient and more accurate measurement to collect than other energy balance measures, such as energy intake. The hypothesised %WC in the face of the current growing obesity pandemic would have clinically relevant impacts on halting the rate of progression of obesity prevalence and mitigating the adverse impacts of adiposity-related disease, simply through shifts in the types of processed in foods being consumed.

Secondary outcomes include changes in dietary intake, waist circumference, body composition (fat mass, fat-free mass), heart rate, blood pressure, cardiometabolic risk factors (comorbidities and blood biomarkers including liver function, lipid profile, glucose, HbA1c and C reactive protein), fasted and fed metabolomics, appetite measures (fasted and fed appetite scores, circulating gut hormones and adipocytokines), sleep, sleep quality, PA levels, physical function (walking distance, leg strength, handgrip strength), mental health, quality of life, well-being and aspects of eating behaviour between MPF and UPF diets, and after the 6-month behavioural intervention compared with the first baseline assessment. In a subset of participants, changes in brain functional resting state connectivity between MPF and UPF diets will be assessed. Further behavioural intervention secondary outcomes include understanding the experiences of UPF versus MPF diets, changes in behaviour regulation and shopping expenditure from the first baseline assessment, and barriers and facilitators to reducing UPF intake.

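### The participant random effect in the primary model, fitted in the usual way, cannot represent a negative correlation between a person's two weight changes; if that correlation is between 0 and about -0.2, the 5% error rate becomes about 5.7% to 7.5%

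*Protocol article*

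**What the plan says.** Three parts of the protocol article bear on this.

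- **Outcome.** The Outcomes section states: "The primary outcome is the mean difference in percent weight change (%WC) at 8 weeks from baseline between MPF and UPF diets". Table 1 (Objectives and hypotheses) adds: "Primary outcome assessed from baseline to 8 weeks follow-up on each diet". Each participant therefore contributes two change values, each measured from the baseline of its own diet period. The periods are separated by a 4-week washout on the habitual diet.
- **Primary analysis.** Statistical methods states: "The primary outcome will be analysed using mixed-effects models, with a random effect for participants". It then lists adjustment covariates. It does not describe the residual covariance, the degrees-of-freedom method or how a variance estimate at zero is handled.
- **Sizing.** Under Sample size, "44 participants are required to detect a mean difference of 2.7% weight change between diets", with "SD of 5.4% (2× the mean difference), power=0.9, alpha=0.05, with a two-sided paired t-test, using SPSS V.27.0". Recruitment is raised to 55 for 20% drop-out.

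The article states no correlation between a person's two weight changes.

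**The concern.** For raw body weights, two readings on one person are strongly and positively correlated, so a participant intercept is harmless. Changes from two separate baselines carry no such guarantee. If weight fluctuates around a personal level, or if those who lost most on the first diet are still regaining during the second, the two changes can be negatively correlated.

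A random intercept with variance at or above zero cannot express this. When the sample covariance is negative, the intercept variance is estimated as zero and the two changes are treated as independent. The variance of their difference is then understated. The effect is anti-conservative, and it falls on the primary test and its confidence interval. The paired t-test behind the sample size has no such restriction, so the sizing method and the analysis method agree on complete pairs only while the estimated covariance is not negative.

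**Working it through.** **1. The plan's own figures reproduce.** The standardised difference is 2.7/5.4 = 0.5. The exact two-sided paired t-test at alpha 0.05 has power 0.9000 with n = 44 and 0.893 with n = 43, so 44 is right. Then 44/(1 − 0.20) = 55. Neither figure depends on the correlation, because the SD of 5.4% is already that of the within-person difference.

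**2. Size of the distortion.** Let each change have variance σ² and let the two have correlation ρ.

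- True variance of the mean within-person difference: 2σ²(1 − ρ)/n.
- Variance assumed once the intercept variance is zero: about 2σ²/n.
- Ratio of model to true standard error: 1/√(1 − ρ). This is 0.953 at ρ = -0.1, 0.913 at -0.2 and 0.877 at -0.3, so the standard error is about 5%, 9% and 12% too small.
- Large-sample error rate when the variance is always zero: 2[1 − Φ(1.96/√(1 − ρ))]. This is 6.2%, 7.4% and 8.6% at the same three values.

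**3. Simulation.** Inputs: 44 complete pairs (from Sample size), no diet effect, diet and period as fixed effects, and 200,000 trials per ρ. The period term and every ρ are assumptions. REML for balanced pairs has a closed form: if the between-person mean square is below the within-person mean square, the residual variance is the pooled mean square; otherwise it is the within-person mean square. The t reference uses the error degrees of freedom of the fitted model: 42 when the intercept variance is positive, 85 when it is zero.

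| ρ (assumed) | Trials with variance at zero | Bounded intercept, t | Bounded intercept, z | Unrestricted, t |
|---|---|---|---|---|
| +0.3 | 2% | 5.0% | 5.7% | 5.0% |
| +0.1 | 26% | 5.2% | 5.9% | 5.0% |
| 0 | 50% | 5.7% | 6.2% | 5.0% |
| -0.1 | 74% | 6.4% | 6.9% | 5.0% |
| -0.2 | 90% | 7.4% | 7.9% | 5.0% |
| -0.3 | 98% | 8.5% | 9.0% | 4.9% |

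Repeat runs differ by about 0.1 to 0.2 points, hence the rounded range of 5.7% to 7.5% for ρ from 0 to -0.2. Keeping 42 degrees of freedom throughout gives 5.5%, 6.1%, 7.0% and 8.1% for ρ = 0 to -0.3. With 54 people the results agree within about 0.3 points.

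**4. Which correlations are plausible?** Suppose weight varies around a stable level with autocorrelation r(t) = exp(−t/τ). The two changes span weeks 0–8 and 12–20, so their correlation is [2r(12) − r(4) − r(20)] / [2(1 − r(8))]. For τ = 8 weeks this is (0.446 − 0.607 − 0.082)/1.264 = -0.19. For τ = 16, 26 and 52 weeks it is -0.15, -0.11 and -0.07. An illustrative regain model, with a half-life of 4–8 weeks and a response SD of 1.5–2.5 points, gives -0.05 to -0.21. None of these time constants or SDs comes from the article. A lasting personal trend, or a stable personal response to taking part, would push the correlation up.

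**The case against.** The strongest reply is that this belongs in a SAP. The article condenses a fuller protocol, a participant random effect is the conventional short description of a cross-over model, and nothing in the text excludes a structured residual or an unbounded variance. That stands against any claim that the plan allows only a non-negative correlation. It does not remove the point, because the one within-person term that is named, fitted with ordinary defaults, behaves as shown above.

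Second, the sign of the correlation is unknown. Both diets are fully provided, ad libitum and supported by the same weekly calls, so a personal response common to both periods is credible and would make the correlation positive. This also stands. At +0.3 the t-based error rate is 5.0%.

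Third, an upper figure of 9% would overstate the matter. It needs a correlation of -0.3 together with a normal reference, whereas the mechanisms sketched here stop near -0.2. About half a point of the z column is the normal reference itself, as the +0.3 row shows. For this reason the t figures are used.

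A reader might also infer from the planning SD that the correlation must be negative. Sample size reports that per-group SDs in other trials ran up to about 0.9 times the mean change, or 0.9 × 2.7 = 2.43%. Combined with 5.4% for the difference, this implies ρ = 1 − 5.4²/(2 × 2.43²) = -1.47, which is impossible. The 5.4% is a deliberately cautious value and is no evidence about the correlation.

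**Conclusion.** The point holds conditionally. With the intercept variance bounded at zero, the primary test is sound when the correlation is clearly positive. It is mildly anti-conservative when the correlation is near zero or negative: about 5.7% at 0, about 7.5% at -0.2, and about 8.5% only at -0.3, against 5.0% for an unrestricted covariance. These figures assume complete pairs, a period term, normal errors and correlations that the article does not supply.

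A reader might infer that the primary standard error is too small, or that sizing by paired t-test contradicts analysis by mixed model. The article supports neither. The first depends on an unknown sign. The second is ordinary practice, and both sizing figures reproduce. This is a low-cost improvement to make before analysis.

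**What to change.** In the primary model, specify an unstructured 2×2 within-participant covariance for the two periods, or compound symmetry allowed to be negative, with Kenward-Roger degrees of freedom. On complete pairs, the compound-symmetry form is the analysis of within-person differences, which matches the basis of the sample size. The unstructured form gives the same result when sequence is in the model and practically the same otherwise. Either form still uses participants who have data from one period only. The same wording can serve secondary outcomes analysed as period changes.

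The cost is one sentence and one or two more variance parameters. With a clearly positive correlation the result is essentially that of the planned model.
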